## Abstract

**Background:**

Dual antiplatelet therapy (DAPT) is recommended in secondary prevention after coronary artery bypass grafting (CABG), but it is inevitably associated with the risk of bleeding, of which gastrointestinal bleeding accounts for more than half. Proton pump inhibitors (PPIs) may increase the risk of major cardiovascular adverse events when reducing the risk of upper gastrointestinal bleeding. Therefore, the optimal duration of a PPI in combination with DAPT is unclear.

**Methods:**

The “Proton Pump Inhibitor Preventing Upper Gastrointestinal Injury in Patients on Dual Antiplatelet Therapy after CABG” (DACAB-GI-2) study is a prospective, single-center, open-label, parallel, randomized controlled trial. A total of 232 eligible subjects who are scheduled or initiated on DAPT (clopidogrel plus aspirin or ticagrelor plus aspirin) for 12 months immediately after CABG will be enrolled and be randomized in a 1:1 ratio to either a 12-month pantoprazole treatment arm or a 1-month treatment arm. The primary outcome is to assess the rate of gastroduodenal erosions and ulcers evaluated by esophagogastroduodenoscopy (EGD) within 12 months after randomization, based on the modified Lanza score. Secondary outcomes include reflux esophagitis and upper gastrointestinal bleeding. Other pre-specified outcomes include major adverse cardiovascular events, graft failure, and all-cause death.

**Discussion:**

This study aims to compare the efficacy and safety of 12 months and 1 month of pantoprazole treatment in preventing DAPT-related upper gastrointestinal mucosal injury after CABG.

**Trial registration:**

ClinicalTrials.gov NCT03908593.

## Background

Dual antiplatelet therapy (DAPT) involving P2Y_12_ receptor inhibitors (clopidogrel or ticagrelor) and aspirin is recommended for secondary prevention after coronary artery bypass grafting (CABG) since 2015 [1]. However, it is associated with an increased risk of gastrointestinal bleeding events [2]. Proton pump inhibitors (PPIs) are the preferred drug for treating gastroduodenal mucosal injury and decreasing the risk of upper gastrointestinal bleeding [3–5]. Regarding the combined use with clopidogrel, previous studies have shown that omeprazole and esomeprazole have competitive inhibition on the CYP2C19 pathway [6, 7]. The guidelines recommend rabeprazole or pantoprazole in combination treatment [8, 9]. Unlike clopidogrel, ticagrelor is a non-prodrug that does not influence the five types of PPI [10, 11].

In 2018, the ESC guidelines recommended (increased from evidence IIa to Ib) a PPI in combination with DAPT treatment [8]. Our previous study (DACAB-GI-1) was a single-center randomized controlled trial (RCT) focused on upper gastrointestinal mucosal injury associated with ticagrelor plus aspirin, ticagrelor alone, or aspirin alone at 1-year post-CABG. The results showed that patients with a history of peptic ulcer and/or gastrointestinal bleeding received more attention, of which 77.7% (7/9) received PPI combination treatment for ≥6 months, while among the patients who received 1 year of ticagrelor plus aspirin therapy after CABG, only 9.9% (8/81) received PPI combination treatment for ≥6 months [12]. The upper gastrointestinal mucosal injury associated with DAPT in patients without a history of peptic ulcer and/or gastrointestinal bleeding needed to be further investigated.

Comparing with capsule endoscopy, the first advantage of esophagogastroduodenoscopy (EGD) is the capability of biopsy [13]. Overt or occult gastrointestinal bleeding in patients on DAPT not only indicates mucosal injury but also is an alarming symptom of gastrointestinal tumors [14, 15]. Pathological biopsy results are the gold standard for determining precancerous or malignant lesions of the esophagus and/or stomach, and whether *Helicobacter pylori* (*H. pylori*) infection is present. Second, EGD can clearly observe the erosion of esophageal mucosa caused by reflux esophagitis (RE), as well as the presence of cardia relaxation and hiatus hernia, which are the pathological structural basis of recurrent gastroesophageal reflux disease [16]. EGD findings could help to rule out esophageal disorders in the differential diagnosis in patients reporting retrosternal discomfort (including chest pain) after CABG. However, capsule endoscopy only remains in the esophagus for a very short time during the examination. Even magnetically controlled capsule endoscopy cannot achieve a subtle examination of several sites, such as the esophagus and cardia [17]. Third, the total medical cost for anesthesia EGD (including pathological biopsy examination) in China is far lower than that of magnetically controlled capsule endoscopy (less than 1/3 of the total cost of the latter) and is included in the national medical insurance coverage.

To date, there has been no study using EGD to compare the differences in upper gastrointestinal mucosal injury after 6 and 12 months of PPI treatment combined with two different DAPT regimens (clopidogrel plus aspirin or ticagrelor plus aspirin). The present study (DACAB-GI-2) intends to compare the efficacy and safety of continuous treatment with pantoprazole for 12 vs. 1 month in preventing DAPT-related upper gastrointestinal mucosal injury after CABG.

## Methods

### Study design

This prospective trial was designed as a single-center randomized, open-label, parallel controlled trial with patients allocated in a ratio of 1:1, to be conducted at the Ruijin Hospital, Shanghai Jiao Tong University School of Medicine, Shanghai, China. The protocol was designed according to the Standard Protocol Items: Recommendations for Interventional Trials (SPIRIT) 2013 Statement.

### Study objectives and hypothesis

The primary objective of the DACAB-GI-2 study is to assess the effect of pantoprazole in the prevention of upper gastrointestinal mucosal injury in patients on DAPT after CABG. The secondary objective is to determine the cumulative incidence of upper gastrointestinal bleeding and major adverse cardiovascular events (MACE). We predicted that patients treated with pantoprazole for 12 months would have a significantly less upper gastrointestinal mucosal injury than patients treated with pantoprazole for 1 month.

### Ethics issues

The present study protocol was approved by the Ethics Committee of Ruijin Hospital, Shanghai Jiao Tong University School of Medicine (No. 2019(43)).

### Participant recruitment

This clinical study was registered on October 20, 2019. Participants will be screened from patients who have undergone CABG at the Cardiac Surgery Department, Ruijin Hospital, after registration. Within 3 days after surgery, patients willing to participate in the study will be carefully evaluated by a cardiac surgeon together with a gastroenterologist based on inclusion and exclusion criteria.

### Criteria

#### Inclusion criteria

Provision of signed informed consent before any study-specific proceduresMale or female, age ≥ 18 years at the time of consentPlanned or initiated the use of 12 months of DAPT (clopidogrel plus aspirin or ticagrelor plus aspirin) immediately following primary isolated elective CABG surgery

#### Exclusion criteria

History of the previous active peptic ulcer within 3 months before enrollmentPlanned use of PPIs to treat acid-associated disorders (e.g., gastroesophageal reflux disease, GERD)Contraindications for aspirin, clopidogrel, ticagrelor, and pantoprazole use (e.g., known allergy)Anticipated concomitant oral or intravenous therapy with strong cytochrome P450 3A4 (CYP3A4) inhibitors or CYP3A4 substrates with narrow therapeutic indices that cannot be stopped for the course of the studyStrong inhibitors: ketoconazole, itraconazole, voriconazole, telithromycin, clarithromycin, nefazodone, ritonavir, saquinavir, nelfinavir, indinavir, and atazanavirCYP3A4 substrates with narrow therapeutic index: quinidine, simvastatin at doses > 40mg daily or lovastatin at doses > 40mg dailyNeed for chronic oral anticoagulant therapy or chronic low-molecular-weight heparinWomen of child-bearing potential who are not willing to use a medically accepted method of contraception that is considered reliable in the judgment of the investigator or women who have a positive pregnancy test at enrollment or randomization or women who are breasting feedingInability of the patient to understand and/or comply with study procedures and/or follow-up, in the opinion of the investigator, or any conditions that, in the opinion of the investigator, may render the patient unable to complete the studyAny condition outside the atherothrombotic study area with a life expectancy of less than 1 yearParticipation in another clinical study with an investigational product within 28 days before enrollment or previous randomization to an investigational product in another ongoing clinical studyAny condition which in the opinion of the investigator would make it unsafe or unsuitable for the patient to participate in this study (e.g., long-term concomitant treatment with non-steroidal anti-inflammatory drugs [NSAIDs])

### Informed consent

Before enrollment, trained researchers will introduce the objective and main aspects of the trial to the patients. Patients will also receive information sheets and then be able to have an informed discussion with the participating consultant. Patients will also be informed of the probable benefits and potential risks and assured that participation is entirely voluntary. Patients who meet all of the inclusion criteria and none of the exclusion criteria will be enrolled after providing written informed consent. The personal information of all participants will always be kept confidential.

### Randomization and allocation

The eligible subjects will be randomized in a ratio of 1:1 to the 12-month or the 1-month pantoprazole treatment group. Block randomization with a block length of four will be applied. The randomization numbers will be generated in a list using SAS 9.4 (SAS Institute Inc., Cary, NC, USA) and sealed in the envelopes (Fig. 1).

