### Blinding

This is an open-label trial.

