### Statistical and analytical plans

The primary analysis was conducted according to the intention-to-treat (ITT) principle. All randomized subjects were included in the ITT analysis set. Subjects who received at least one dose of study medication and continued to receive the randomized intervention regimen (with or without study medication) 1 month after CABG were defined as the modified full analysis set (mFAS) population. Among them, subjects who completed the treatment according to the randomized protocol without major protocol violations and had a primary outcome assessment were included in the per-protocol set. Effectiveness analysis will be performed on the basis of mFAS. The safety analysis set consists of all the subjects who had taken at least one dose of study medication.

In this study, all subjects received pantoprazole treatment for at least 1 month after CABG. Due to the COVID-19 pandemic, some subjects are unable to return to the center for study drugs and/or follow-up 1 month after the randomization. Those subjects who are unable to receive subsequent randomization intervention will be excluded from the mFAS and not included in the effectiveness analysis. Considering the statistical power of the study, randomized subjects will be added until the effective randomized intervention number reaches the predetermined sample size.

All statistical analyses will be performed using SAS version 9.4 (SAS Institute Inc. SAS/STAT, Cary, NC, USA). Unless specified otherwise, the number of subjects (*n*), mean, standard deviation, median, maximum, and minimum will be provided for continuous variables, and the number of subjects and the percentage will be provided for categorical variables.

The baseline in this study will be defined as the last available (non-missing) assessment (scheduled or unscheduled) before or on the same day as the first dose of study treatment.

The chi-square test will be applied as the main analysis of the primary efficacy endpoint, and multiple sensitivity analyses will be performed to support the main analysis. For secondary and exploratory efficacy endpoints, analysis of covariance, Wilcoxon-Mann-Whitney test, log-rank test, a mixed-effects model for repeated measures, and negative binomial regression model will be applied based on the type of data in the analysis. Descriptive statistics will be provided to summarize safety endpoints.

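### A constant block length of four in an open-label, single-centre trial leaves an expected third of allocations deducible by staff who know the length and see past allocations

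*Protocol article*

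**What the plan says.** All places are in the Protocol article.

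- Randomization and allocation: patients are split equally between the two pantoprazole durations. One constant block size is fixed: "Block randomization with a block length of four will be applied". Allocations come from a SAS list and are "sealed in the envelopes". No second block size and no stratification factor is stated.
- Study design: one centre, so one site can see the whole sequence. Blinding: "This is an open-label trial".
- Participant recruitment: a cardiac surgeon and a gastroenterologist at the site judge eligibility jointly, in the first three days after the operation. Two of the exclusion criteria are open-ended and rest on the investigator's opinion. Another turns on planned PPI use for acid disorders.
- Follow-up: the endoscopist is blinded to allocation.
- Statistical and analytical plans: recruitment stays open, because "randomized subjects will be added until the effective randomized intervention number reaches the predetermined sample size".
- Trial status: 236 enrolled by February 2022, 183 of them with an effective randomized intervention, 117 with completed 12-month follow-up, and completion planned for June 2023.

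**The concern.** In permuted blocks of known constant length, the end of each block follows from its beginning. Sealed envelopes stop anyone reading ahead, but they do not stop deduction from envelopes already opened. With open treatment at a single site, the people who judge eligibility may be the people who can count.

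The plan gives some reason for recruiters to have a preference. The Study objectives and hypothesis section predicts that 12 months is better. The Background reports that in the group's earlier trial 7 of 9 patients with ulcer or bleeding history had a PPI for six months or more, against 8 of 81 on ticagrelor plus aspirin. Patients with an older ulcer history can still enter, because only active ulcer within three months is excluded.

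If patients at higher gastric risk were entered preferentially when one arm was due, the arms would differ at baseline in what drives the primary outcome. Blinded reading of endoscopies cannot undo that. There is no baseline endoscopy, so a difference in mucosal injury at entry would not be seen directly, and the main analysis is a chi-square test.

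**Working it through.** The plan gives no figure for predictability, so there is none to reproduce. Its sample size does not bear on this point.

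**Inputs.** Block length 4 and ratio 1:1 (Randomization and allocation); 236 enrolled and 183 effective (Trial status); 186 required and 232 after the drop-out allowance (Sample size). Assumption: all 236 enrolled were randomized from this list.

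**Allocations known with certainty.** A 2+2 block has six equally likely orders.
- Four orders (ABAB, ABBA, BABA, BAAB) leave only the last place determined.
- Two orders (AABB, BBAA) leave the last two places determined.
- Expected number per block = (4×1 + 2×2)/6 = 4/3. Share = (4/3)/4 = 33.3%.
- Over 236 allocations: 236/3 = about 79. The fourth place alone accounts for 236/4 = 59.

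**Best guess.** Always guess the arm with more places left, and toss a coin when equal.
- Place 1: 1/2. Place 2: 2/3. Place 3: (1/3)×1 + (2/3)×(1/2) = 2/3. Place 4: 1.
- Sum = 17/6 per block. Success = (17/6)/4 = 17/24 = 70.8%.

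**Allocations still to come.** The text does not say whether the target for effective subjects is 186 or 232.
- Effective rate so far = 183/236 = 77.5%.
- Target 186: (186 − 183)/0.775 = about 4 more.
- Target 232: (232 − 183)/0.775 = about 63 more.

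**What other schemes would give.** Fixed sizes are by enumeration. Mixed sizes are by simulation of sequences of 232, with sizes equally likely and a recruiter who knows the set of sizes and uses all past allocations. The sizes themselves are illustrative assumptions.

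| Scheme | Known with certainty | Best guess correct |
|---|---|---|
| Fixed 4 (plan) | 33.3% | 70.8% |
| Fixed 6 | 25% | 68.3% |
| Fixed 8 | 20% | 66.6% |
| Mixed 4/6 | about 5% | about 69% |
| Mixed 4/6/8 | about 2% | about 68% |

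Mixing sizes nearly removes certainty but barely lowers guessing success. Keeping sequence knowledge away from recruiters therefore matters as much as the block sizes.

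**The case against.** The strongest reply is that the one third is conditional. It needs recruiters who know the length, see each opened envelope and track block boundaries. The article does not say who holds the list or opens the envelopes. The full protocol (version 4.0) is not shown and may settle this, and may also state stratification. This stands, and it is why custody is something to confirm and not a fault.

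Other parts also stand:
- The article reports the 236 as already enrolled, so its publication cannot have told their recruiters the block length.
- Both arms take pantoprazole in the first month, so drug use does not separate them then. At 236/28 = about 8 patients per month, roughly two blocks pass before it does. Only someone who sees the envelope result can count in real time.
- Two specialists judge eligibility jointly within three days of surgery, while patients arrived on average every three to four days (about 850 days/236 = 3.6). Changing the order would often not change the slot, though exclusion on opinion remains possible.
- The motive is softened. Planned PPI use for acid disorders is excluded, and control patients have other gastric medication available and listed triggers for continuing a PPI.
- The figure of 63 is an upper bound that fits the calendar poorly. It needs 63/8.4 = about 7.5 months of accrual after February 2022, whereas 12-month follow-up ending in June 2023 implies last entry around June 2022.

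It does not stand that this is merely detail left to the analysis plan. The constant block length is a stated design choice. The promise of multiple sensitivity analyses does not name this one.

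A reader might infer that recruiters did know a third of allocations, or that the primary comparison is biased. The document supports neither. It shows no steering, and the baseline data collected (Scope of study data) would make some imbalance visible.

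**Conclusion.** The point holds as a design weakness that makes selection bias possible, not as evidence of bias. Its size is an expected 33.3% of allocations deducible and 70.8% guessable, for staff who know the block length and see past allocations in order. If recruiters never see the opened envelopes, the exposure in month 1 largely disappears. If allocation was stratified, counting would have to be done within strata and would be harder. It is a worthwhile improvement and does not invalidate the trial. If the target is 186, few allocations remain and the check on the 236 carries most of the value.

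**What to change.** **Further subjects.** Generate a new list with randomly varying block sizes, do not disclose the sizes to recruiters, and confirm that the list is held outside the recruiting team. State whether the target for added subjects is 186 or 232.

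**The 236 already enrolled.** Before outcome data are complete, pre-specify one sensitivity analysis:
1. From the list and enrolment order, compute each patient's probability of the 12-month arm given earlier allocations in the block (0, 1/3, 1/2, 2/3 or 1), following Berger-Exner.
2. Test its relation to the primary outcome within each arm, and to baseline *H. pylori* status, medical and medication history, and haemoglobin.
3. Report the primary result adjusted for it. Patients at 0 or 1 occur in one arm only, so the adjustment leans on the model there. Say so in the report.

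**Cost.** A protocol amendment with ethics approval (section Amendment), a new list, a possible arm imbalance of a few patients, and one extra table. The check has limited power, so a null result would not prove that no steering took place.

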**Fig. 1 Fig1:**
[figure not shown]
Trial flow diagram

### Blinding

This is an open-label trial.

### Intervention

Participants will be equally randomized into two groups: the experimental group (12-month treatment of pantoprazole) or the control group (1-month treatment of pantoprazole). Pantoprazole, 40 mg daily, will be used in combination with two different DAPT regimens (clopidogrel plus aspirin or ticagrelor plus aspirin), respectively. The study drug will be provided by Takeda (Shanghai, China). The detailed study schedule is listed in Fig. 2.

**Fig. 2 Fig2:**
[figure not shown]
Schedule of enrollment, interventions, and assessments for the trial

Relevant concomitant interventions that are permitted or prohibited during the trial: The medication for secondary prevention after CABG may follow the guidelines for cardiovascular disease. The use of anti-dyslipidemic, anti-hypertensive, and anti-diabetic medications is permitted. If the following two situations occur, it will not be regarded as a violation of the study protocol: (1) The cumulative number of days that a patient has taken double doses of PPI should not exceed 1 month. (2) The cumulative number of days that a patient has taken NSAIDs should not exceed 2 months. In the present study, patients randomized in the 1-month pantoprazole treatment group are allowed to take histamine-2 receptor blocker or gastric mucosal protective agents as needed after withdrawal of pantoprazole. However, patients randomized in the 12-month pantoprazole treatment group are prohibited to use the above medication. If a patient receives *H. pylori* eradication therapy and the second urea breath test within the 12 months after randomization, he should report to the investigator.

### Data capture

The case report form (CRF) will be finalized and the electronic database will be established based on CRF before the enrollment of the first subject. All required study data must be recorded in the CRFs. The training on CRF implementation will be provided to all the staff on the site, including instructions on how to address missing data, corrections, query procedures, and signatures. For those subjects who withdraw before completion of the study, all available efficacy and safety data must be recorded in the CRFs. Incomplete or inconsistent data on the CRFs will result in data queries addressed to the investigator for resolution.

### Follow-up

Patients will be followed up to 12 months post-randomization unless dead. The outcome will be collected at 2±1 day, 9±2 days, 1 month (30±7 days), 3 months (90±7 days), 6 months (180±14 days), 9 months (270±14 days), and 12 months (360±14 days) after CABG surgery, respectively. Among them, the visits at 3 and 9 months after randomization are telephone calls. Each subject’s survival status (surviving/deceased), blood pressure, heart rate, body mass index, waist circumference, and adverse events (AEs) will be recorded on the CRF after each conversation. At 6 and 12 months post-randomization, routine laboratory tests and anesthesia EGD will be performed respectively. The endoscopist in the present study who evaluated the upper GI mucosal injury was blinded to random treatment allocations. In addition, computed tomographic angiography (CTA) or coronary angiography (CAG) is also required at 12 months post-randomization. Face-to-face adherence reminder sessions will take place at the initial pantoprazole dispensing and each study visit thereafter.

